## Abstract

**Background:**

Risk of new episodes is a constant concern for people living with bipolar disorder (BD). Research into sleep and circadian rhythm disruption (SCRD) suggests that relapse risk may be measurable in 24-hour rest-activity rhythms (RAR) via actigraphy. The primary aim of the Tipping Point project is to develop an algorithm forecasting relapse based on RAR. A secondary aim is to explore SCRD mechanisms linking RAR to mood dynamics in BD. The mechanistic investigation involves analysis of biological correlates of RAR, and exploration of system instability as a predictor of two types of state transition (relapse and recovery).

**Method:**

Three prospective studies will enrol adults living with BD I or II. Study 1 (Australia) recruits
*N* = 100 individuals with interepisode BD who will undergo three contiguous 26-week monitoring epochs. Each epoch commences with 14 days of actigraphy, followed by retrospective interviews at 13 and 26 weeks. RAR predictors of time to first relapse will be explored using three computational frameworks - statistical risk, probabilistic network graphs and non-linear dynamic models. Study 2 (India) replicates one of the 26-week epochs of Study 1, recruiting 25 individuals with BD and 25 matched healthy controls. Study 2 investigates the replicability of models identified in Study 1 and tests the mechanistic association between amplitude of the RAR and amplitude of clock gene expression. Study 3 (New Zealand) explores system instability as a mechanism, by investigating whether complex system indicators of relapse risk (from Study 1) also forecast recovery from acute episodes. In Study 3, actigraphy data will be collected from people experiencing a severe episode of BD depression (
*N* = 30) or mania (
*N* = 15).

**Discussion:**

The Tipping Point project uses a multi-study design to develop a mechanistically-informed predictive algorithm for relapse risk in BD.

## Introduction

1.

Bipolar disorder (BD) is a serious episodic mood disorder associated with significant morbidity and mortality.
^
1
^ The psychological, familial, social, and clinical burden of BD is reflected in its economic cost.
^
2
^
^,^
^
3
^ In Australia, the excess health care costs of BD are about AU$7.3 billion per annum.
^
4
^ It is estimated that three-quarters of this cost could be saved with improved management, particularly avoidance of hospitalisation via early warning of impending relapse.
^
4
^ The present project takes up the challenge of improving forecasting of the short-term course (weeks and months) of BD, with the clinical aim of identifying an algorithm for BD relapse risk based on rest-activity rhythms (RAR).

The course of BD remains poorly understood, but we do know it is highly heterogeneous within and between individuals,
^
5
^ and clinical characteristics (prior course, residual symptoms, etc.) are only modest predictors of relapse and recurrence.
^
6
^ Emerging computational approaches have great potential to improve understanding of the course of mood disorders, with models ranging from purely data-driven [e.g.,
7,
8] to theoretically-informed [e.g.,
9,
10]. Here, the latter approach is prioritised, leveraging off rapidly growing understanding of sleep and circadian rhythm disruption (SCRD) in psychopathology.
^
11
^
^,^
^
12
^

The SCRD framework has unique strengths as an explanatory approach to BD. First, recent reviews highlight evidence for SCRD involvement in BD’s development and course, and specifically that SCRD variables may act as predictive biomarkers.
^
13
^
^–^
^
15
^ Secondly, an associated passive data collection methodology – 24-hour rest-activity rhythms (RAR) measured by actigraphy – supports investigation of chronobiology in the real world.
^
16
^ Furthermore, actigraphy is non-invasive and inexpensive, and could potentially translate to an automated early warning tool.
^
17
^
^,^
^
18
^

The primary aim of this project is to develop an SCRD-informed, RAR based algorithm forecasting relapse risk in BD. Confidence in the reliability and generalisability of a predictive algorithm would be strengthened with improved mechanistic understanding of SCRD in BD as measured by RAR in this forecasting context. Consequently, the project’s secondary aim is to contribute to mechanistic understanding by, (i) investigating molecular biological correlates of RAR parameters, and (ii) exploring system instability as a predictor of both relapse into, and recovery from acute episodes (with both phenomena understood as transitions in state space [e.g.,
19]).

### Introduction to the Circadian System and Sleep

1.1

Evolution on earth has favoured organisms that anticipate, rather than react to, the planet’s daily shifts between light and dark. The embodiment of this ‘predictive homeostasis’ is the circadian system, which coordinates internal physiology and environmental activity in most species.
^
20
^ The adaptive endpoint of biological clockwork is circadian (approximately 24-hour) rhythmicity in biological (e.g., core body temperature), behavioural (the activity-rest cycle), and mental (attention, affect) processes.

The molecular genetics of circadian rhythmicity is well characterised in mammals.
^
21
^ Within the master oscillator of the suprachiasmatic nucleus (SCN), self-sustained rhythmicity is generated by a primary intra-cell autoregulatory transcription-translation feedback loop (TTFL) involving the activators CLOCK and BMAL1, and their target genes
*PER1, PER2, CRY1* and
*CRY2*, whose products form a negative-feedback repressor complex [additional stabilisation and auxiliary loops interlock with this core process,
22]. Similar cellular clocks operate throughout the body, receiving inputs from the SCN to coordinate internal timing across tissues: Diurnal variation in clock gene expression in red blood cells, for example, has been used as an indicator of circadian amplitude and phase.
^
23
^
^,^
^
24
^ The secondary mechanistic aim of the present project includes investigation of the association between blood-based circadian markers (gene expression and associated metabolites) and RAR parameters.

From a circadian viewpoint, the sleep-wake cycle is the most visible circadian rhythm in humans.
^
25
^ From the viewpoint of sleep
*per se*, the circadian system is one of two primary drivers of sleep timing [the other being a homeostatic sleep drive,
26]. Parsing circadian from sleep processes in humans is a methodological challenge, traditionally addressed by sleep-disrupting laboratory protocols that are unsuitable for people with BD.
^
27
^ As discussed below, contemporary translational research is increasingly using passive data collection and computational methods to study these processes in everyday life.

### Sleep and Circadian Rhythm Disruption may be a Predictive Biomarker in BD

1.2

Sleep and circadian rhythm disturbances are common symptoms of BD episodes but have also been shown to precede full-threshold episodes [e.g.,
28–
33]. For example, candidate gene association studies provide some support for associations between BD and common variants in
*CLOCK* [the ClockΔ19-mutant mouse is the best-characterised animal model of BD,
34], and variants of
*ARNTL* [see, for a review,
15]. A recent international expert review concluded that SCRD plays an important role in mental health, but causal pathways remain poorly understood.
^
35
^ In mood disorders, several SCRD pathways have been proposed to be mechanistically important.
^
36
^
^–^
^
38
^ For example, decreased robustness of circadian rhythmicity – measurable in decreased amplitude of downstream RAR – may be an endophenotype of BD [e.g.,
13,
15,
39–
42].

### Actigraphy

1.3

Actigraphy was originally used to measure sleep patterns, where it has been shown to be reliable and valid,
^
43
^ including amongst individuals with BD.
^
44
^
^,^
^
45
^ The last decade has seen rapidly increasing interest in actigraphy due to: (i) recognition of activity disturbance as core to the BD phenotype
^
46
^
^,^
^
47
^; (ii) its promotion by the US National Institute of Mental Health as a method for investigating arousal and regulatory systems
^
48
^; (iii) growing research into digital phenotyping and passive sensing via wearables,
^
49
^
^–^
^
52
^ and (iv) emerging personalised models of psychopathology.
^
8
^
^,^
^
53
^

Polysomnography (PSG) is the gold standard measure of sleep patterns and circadian markers of sleep-wake cycles. However, studies using actigraphy are overtaking PSG as the former offers an ecologically valid measurement of individual chronobiological functioning in everyday life.
^
54
^ Actigraphy research in BD has moved beyond the analysis of sleep parameters generated from the manufacturers’ software programmes (e.g., mean and standard deviation estimates of total sleep time, sleep onset latency, sleep efficiency, wake after sleep onset) to include estimation of RAR parameters that may be more critical for mental disorders such as stability, variability or predictability of 24-hour sleep-wake cycles and the regularity of timing of activity.
^
55
^ Other work in BD has investigated actigraphy as a measure of chronotype [often delayed in BD compared to healthy controls,
54] and a range of sleep timing variables.
^
56
^

Prominent in this RAR work are three non-parametric variables originally proposed by Van Someren and colleagues: Relative Amplitude, Intradaily Variability, and Interdaily Stability.
^
57
^ Amongst these ‘Van Someren variables’, Relative Amplitude is of particular interest in this project. Understood as a measure of circadian robustness, Relative Amplitude (the difference between most and least active periods compared with total activity per 24 hours) has been associated with a range of BD phenotypes and outcomes.
^
16
^

Actigraphy generates a high-resolution data stream (14 days’ recording generates 1.2 million data points), supporting a range of analyses, including but not limited to the macro-level sleep and circadian proxy variables introduced above [see,
54]. Actigraphic measurement figures prominently in computational models of mental health,
^
58
^
^,^
^
59
^ and mood disorders particularly [e.g.,
60,
61]. The present project uses three complementary frameworks to advance prediction of BD course from RAR – statistical risk (Cox Survival Analysis), probabilistic network graphs (Dynamic Bayesian Network Analysis) and non-linear dynamic analysis (Hadaeghi’s Complex System Model of BD,
19). The RAR measures to be modelled as predictors in these analyses include the three non-parametric Van Someren variables (above). Relative Amplitude is elevated as a correlate of circadian biology in the mechanistic investigation of Study 2 (see below).

*Actigraphic Measurement of the 24-h Rest-Activity Rhythm can Predict Course of BD*

A substantial body of research has investigated
*cross-sectional
* associations between actigraphy-measured RAR variables and BD phenotypes. A recent systematic review identified 70 studies investigating RAR via actigraphy in BD samples.
^
16
^ Attenuated amplitude of RAR has been shown to associate with several BD phenotypes.
^
62
^
^–^
^
64
^ Consistent with the circadian robustness hypothesis (above), the largest study to date
^
31
^ found that a one quintile (20%) decrease in Relative Amplitude was associated with a small but significant increased risk of lifetime major depressive disorder (OR 1.06, 95% CI 1.04–1.08) and lifetime BD (OR 1.11, 1.03–1.20) [
1].

Several groups have argued for the potential of RAR signals to generate a clinically-useful predictive algorithm of short-term course in mood disorders and BD specifically.
^
10
^
^,^
^
16
^
^,^
^
18
^
^,^
^
43
^
^,^
^
66
^
^–^
^
68
^ Prospective empirical investigations are limited to date, but an illustrative example is the study of Ferrand and colleagues, in which RAR was sampled with 14 days actigraphy data before 69 euthymic individuals with BD were prospectively tracked for a median duration of 3.5 years.
^
69
^ Approximately 65% of participants experienced a relapse or recurrence during follow-up. After adjusting for key clinical variables (age, sex, BD subtype, number of mood stabilisers, etc.), time to episode onset was predicted by an actigraphy dimension comprising amplitude and variability/stability of circadian rhythms (
*p* = 0.009). The area under the curve (AUC) was improved from 0.64 for clinical predictors alone to 0.82 with the addition of actigraphy-derived Intradaily Variability (
*p* = 0.04).

A recent evidence-map review of prospective studies by Scott and colleagues investigated actigraphy parameters as predictors of course, outcome, and treatment response in BD.
^
55
^ Scott et al. conclude actigraphy markers have potential to predict future mental state, with the strongest individual predictors being attenuated amplitude and delayed sleep onset. The authors note significant limitations in existing literature, including small sample sizes, varied endpoints, and an unsystematic approach to covariates and statistical modelling.

### The Tipping Point project

1.4

The Tipping Point project is fundamentally exploratory. Its primary aim is to
*develop and cross-validate an RAR algorithm of relapse risk for BD.* The algorithm could form the basis of a future actigraphy-based early warning device for people living with BD. The project applies three analytic frameworks (see
2.2 and
2.6 below) to develop predictions of BD course from RAR – statistical risk (Cox Survival Analysis), probabilistic network graphs (Dynamic Bayesian Network Analysis) and non-linear dynamic analysis (Hadaeghi’s Complex System Model of BD).

The project’s secondary aim is to contribute to improved mechanistic understanding of SCRD in BD as measured by RAR in this forecasting context. Consistent with the brief literature review above, two types of mechanism warrant investigation. First, to ground the actigraphy signal in circadian biology, RAR parameters will be correlated with circadian gene expression patterns amongst people with BD and a matched control sample. Second, by conceptualising relapse in non-linear dynamic terms as a state transition, we explore whether Hadaeghi’s Complex System Model
^
19
^ applied to prediction of
*relapse* generalises to prediction of an alternative clinically significant state transition, namely,
*response to treatment* for an acute episode.

The project involves four work packages. Three of these are prospective empirical studies amongst people living with BD. Study 1 (WP1, Australia) aims to predict early relapse by modelling RAR data. Study 2 (WP2, India) tests predictive models from RAR developed in Study 1 and tests the mechanistic relationship between a key RAR variable (Relative Amplitude, representing circadian robustness) and diurnal amplitude of gene expression and metabolites in blood. Study 3 (WP3, New Zealand) advances mechanistic understanding of the link between RARs and mood in BD by investigating a different state transition, namely, recovery from an acute episode, operationalised in response to evidence-based treatment. Thus, Studies 1 and 2 contribute to the project’s primary aim of algorithm development, and Studies 2 and 3 contribute (in different ways) to the secondary aim of improved mechanistic understanding of RAR variables in predicting BD course. Finally, WP4 is computational, conducting model comparison, cross-validation and synthesis using ensemble machine learning. A key output of WP4 is an open dataset and computational pipelines for sharing with future researchers.

## Protocol

2.

To ensure clarity and appropriate detail for a project with this hierarchical structure, a multi-paper registration strategy has been adopted. Study-specific methodological details essential for direct replication of each component (e.g., detailed assessment schedules, site-specific recruitment procedures, and embedded sub-studies) will be provided in three forthcoming, cross-referenced study-level protocols [
2]. This manuscript presents the overarching project protocol, detailing the scientific rationale, the high-level design of the three empirical studies, and the cross-study analytic plan (WP4).
Box 1 provides an overview and comparison of the three studies’ methods.

Box 1. Comparison of methods across three empirical work packages.**Table T1:** 

Design Feature	Study 1 (Australia)	Study 2 (India)	Study 3 (New Zealand)
Primary Aim	Develop and train a predictive model for relapse risk from RAR data.	Replicate the relapse model in a low-middle income context and test biological correlates of RAR.	Test generalisability of the relapse model to predict treatment response (recovery).
Population	Adults with interepisode BD I or II.	Adults with interepisode BD I or II, plus matched healthy controls.	Adults experiencing an acute manic or depressive episode of BD I or II.
Setting	Outpatients/Community recruitment.	Outpatients/recruitment via hospital-based clinicians.	Predominantly inpatients, some outpatient recruitment via clinicians.
Primary Predictor	Actigraphy (RAR variables) over 14 days (at baseline of three epochs).	Actigraphy (RAR variables) over 14 days (at baseline of one epoch).	Actigraphy (RAR variables) over 14 days (at baseline).
Primary Outcome	Time to Relapse over three 26-week epochs (measured via retrospective LIFE interview on two occasions per epoch).	Time to Relapse over a 26-week epoch (measured via retrospective LIFE interview on two occasions over 26 weeks).	Treatment Response (≥50% symptom reduction) at 8 weeks.
Biological Sampling	No	Yes (blood samples) for circadian gene expression and metabolomics.	No
Clinical Predictors in models	Yes (five key clinical variables included as covariates, e.g., BD subtype, residual symptoms).	Yes (five clinical variables included to enable direct replication of Study 1).	No (to minimise participant burden in an acutely ill population).
Contribution to project	Core model development and initial validation.	Cross-cultural replication and mechanistic analysis via biological correlates.	Mechanistic analysis via testing of model generalisation from one form of state transition (relapse) to another (recovery)

### Inclusion and exclusion criteria

2.1

The approach to sampling and inclusion/exclusion balances four principles: maximising generalisability of findings, maximising inclusivity for people living with BD, participant empowerment and duty of care.

*All studies*

In all studies, participants must have a diagnosis of BD I or II confirmed by structured clinical interview. Reason to believe that participation would interfere with treatment and/or recovery is an exclusion criterion. Participants must have sufficient language fluency (English in Studies 1 and 3; English, Hindi, Telegu, or Bengali in Study 2) to be able to provide informed consent and to complete self-report and interview-based assessments. Age range for inclusion is 18–65 years. This range was selected to limit variance associated with the distinct circadian and sleep changes of adolescence and later life and is conventional for operationalising the ‘adult’ life phase in mental health research. Similarly, age 65 is a common cut-off in BD [e.g.,
70] and sleep/circadian research [e.g.,
40].

Presence of a physical problem that might confound RAR interpretation is an exclusion. The decision about whether to exclude is made case-by-case, considering the sampling principles of generalisability and inclusivity (above). Screening for this exclusion differs by study. In Studies 1 and 2, participants are asked at screening about any physical conditions that impact movement, which are then followed up at interview. In Study 3, nurses involved in recruitment are trained to observe for movement (particularly Parkinsonian tremor in the inpatient setting) as a potential exclusion.

Presence of common BD comorbidities is not an exclusion criterion. Anxiety disorders, substance use disorders and sleep disorders will be assessed by structured clinical interview at baseline and explored for potential inclusion in predictive models. This approach allows us to build models that generalise to complex clinical presentations while still accounting for their impact on models.

*Study 1 and 2*

In Study 1 and 2, being in an episode
*at baseline* is an exclusion criterion. Following common cut-offs [e.g.,
71,
72] presence of an episode is defined as a score of > 12 on the Montgomery-Asberg Depression Rating Scale [MADRS,
73], or > 8 on the Young Mania Rating Scale [YMRS,
74] [
3]. Meeting episode criteria at one of the follow-up interviews is, however, not an exclusion criterion. Considering patient empowerment, risk management and the scientific aims of tracking BD course over an extended period, it was decided on balance to make case-by-case decisions on whether ongoing participation is affected by identification of an episode at a follow-up interview (see below) [
4].

On duty of care grounds, clinical participants in the outpatient Studies 1 and 2 must be currently receiving treatment for BD from a medical practitioner and provide contact details and consent for the doctor to be contacted if required. An additional exclusion criterion in Study 1 and 2 is the presence of active suicidality, measured at baseline and at each follow-up interview. Because of blood draws, a further exclusion criterion in Study 2 only is severe anaemia (Hb level < 7 g/d).

*Study 3*

Study 3 is distinct from Studies 1 and 2 in population, setting and primary outcome (
Box 1). Being in a severe episode of mania or bipolar depression is an inclusion criterion, as defined by a Clinical Global Impression Scale [CGI,
76] of 5 and above, and the majority of participants will be recruited as inpatients. Current intoxication or withdrawal from illicit substances are exclusions unique to Study 3: it is not uncommon for individuals to be admitted to hospital in a state of intoxication or acute withdrawal (e.g., from alcohol or methamphetamines). These states would profoundly impact the capacity to consent and confound the actigraphy data collected in the initial days.

*Written and Informed Consent*

In all studies, written informed consent will be obtained from each participant after they receive detailed explanations about the study procedure in the language best understood by them. Participants can withdraw from the study at any time but will not be able to withdraw data already provided. Participants will be invited to provide ‘extended’ consent so that data can be shared with appropriate research teams upon completion of this project. All participants will be assigned a study ID to be used in place of the participant’s name on all assessment materials. The list linking IDs and names will be held under the same security conditions as study data (see below).

### Work packages

2.2

Three prospective monitoring studies are planned as three work packages. A fourth integrative work package will synthesise mechanistic and modelling findings from Studies 1–3 and develop the theoretically-informed relapse risk algorithm for testing in future independent samples.

*Study 1: Predicting relapse in interepisode BD from rest-activity rhythms*

Study 1 (Australia) provides the primary 18-month dataset on which to conduct Cox Survival Analysis, develop Dynamic Bayesian Network models predicting evolution of symptoms and full-threshold relapse, and to train/test Hadaeghi’s Complex System Model. A total of
*N* = 100 individuals with BD will wear actigraphs for 14 days at the start of each of three consecutive 26-week monitoring epochs (for a total window of 3 × 26 = 78 weeks forecasting, see
Figure 1). In Study 1 (and Study 2), time to relapse will be measured on the retrospective LIFE interview
^
77
^ conducted at 13 and 26 weeks of each epoch. We propose that 26 weeks is a clinically meaningful timeframe for the present interest in course across weeks and months, as it generates translatable information for use in clinical settings (e.g., at initial assessment, or at the transition from inpatient to outpatient management).

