### Primary outcomes

2.4

*Study 1 and 2: Time to relapse*

In Study 1 and 2, the time to relapse of any BD episode (manic, hypomanic, depressive) will be assessed using the LIFE [
5]. The LIFE was developed to retrospectively assess the longitudinal course of psychiatric disorders over extended periods. Weekly data are elicited retrospectively, in an interview format. The method allows for the overall quantification of mood burden, through the interviewer determining ordinal weekly scores for severity of depression and mania. Patients are rated on a 1–6 scale, where 1—no symptoms, 2—residual symptoms, 3—partial remission, 4—does not meet DSM criteria but has major symptoms or impairment, 5—meets definite DSM criteria for an “episode”, and 6—fulfills definite criteria for an “episode” with the presence of either psychotic symptoms or extreme impairment in functioning. By determining whether syndromal symptoms last 2 weeks, relapse into a depressive or manic episode can be determined. The LIFE method has been used in several longer-term studies in BD to determine time to episode occurrence and overall mood morbidity [e.g.,
79–
82]. The retrospective LIFE avoids the problem of participant burden with prospective (e.g., weekly or monthly) measurement in long-term outcome research, and in BD populations has the additional strength of minimising the confound of episode-related impaired insight. Porter and colleagues have recently published an analysis of two studies validating the LIFE’s retrospective weekly estimates against concurrently rated clinician ratings on the MADRS and YMRS.
^
72
^

In Study 1 and 2, LIFE interviews will occur twice in each monitoring epoch (13 weeks, and 26 weeks, with 13 weeks’ retrospection window at each interview). The LIFE is commonly administered at 6-month intervals, and there is reason to believe that the 13-week intervals here will improve the reliability and resolution of our estimate of time to relapse.
^
71
^
^,^
^
77
^ Because of remote recruitment, the LIFE will be conducted by telehealth in Study 1. In Study 2, the LIFE will be conducted in person.

In Study 1 and 2, two types of secondary analysis will be conducted. First, recognising that the number of observed relapses may not be sufficient to support reliable modelling, a secondary analysis will be conducted on the prediction of

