To minimise the impact of any adverse events in Study 1 and 2, being under the ongoing care of a nominated medical practitioner is an inclusion criterion. In Study 1, once participants consent, an email will be sent to their practitioner noting that the patient has enrolled in the study, that the researchers are not taking over their care, and that the provider will potentially be contacted should the researchers become aware of crisis or risk. At each follow-up assessment interview, clinicians’ contact details will be updated if required and suicidality checked by re-administering the CSSRS.

Four specific risk management processes of Studies 1 and 2 are noteworthy. First, active suicidality (operationalised as CSSRS of 3, 4 or 5) is an exclusion criterion, as is reason to think that participation might compromise care. People who are at baseline or become ineligible due to active suicidality will be provided with support and referred back to their clinician. On a case-by-case basis, people excluded because of active suicidality may be invited to recontact researchers once treatment and symptom stability are in place.

Second, as noted above, meeting MADRS or YMRS episode criteria (> 12 and > 8, respectively) is an exclusion criterion at baseline. Following a protocol we have used previously to balance risk management with lived experience empowerment,
^
20
^ potential participants who are in an episode at baseline, but meet all other criteria for the study will be offered the option of being recontacted in 4 weeks to see if they would like to repeat the eligibility assessment (‘re-assessed’).

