## Discussion

3.

The Tipping Point project is conducted at a time of growing scientific interest in SCRD, wearables and computational approaches in mood disorders. A key driver of this interest is the potential for clinically translatable tools. The present project takes up this challenge and has two linked aims. The primary aim is to develop a relapse risk algorithm for people living with BD. The algorithm has translational potential, because actigraph technology is non-invasive, cheap and acceptable to people with BD. The project’s secondary aim is to increase confidence in the derived RAR algorithm by improving mechanistic understanding of RAR-measured SCRD involvement in BD. The underlying mechanisms of RAR-based prediction of relapse risk will be illuminated by, (i) testing the association between RAR parameters and molecular biological measures of circadian function, and (ii) investigating whether a complex systems model of relapse risk can also predict another state transition in BD – recovery from an acute episode.

The project has several strengths. First, it is highly interdisciplinary, with team members bringing expertise in psychology, psychiatry, statistics, computational biology, molecular biology, and behavioural analyses. Second, our long-standing lived experience collaborators have been influential in developing the grant application, the present protocol, and remain active in data collection, governance, and translation of findings. Growing from our work in participatory research [e.g.,
70,
110,
111], an assumption of the project is that participants are also collaborators in, rather than subjects of, the research: participants are properly remunerated for their time and will be consulted on project findings to inform next steps. Third, the project compares data from Australian and Indian samples: whilst the latter sample is of modest size, the project is an important first attempt to see if modelling findings replicate beyond high-income countries.
^
112
^ Finally, the person-days of Study 1 (
*N* = 14 days X 3 epochs X 100 participants = up to 4,200 actigraphy days;
*N* = 7 days X 26 weeks X 3 epochs X 100 participants = up to 54,600 follow-up days) make it to our knowledge the largest prospective investigation of actigraphic predictors of BD course to date.

Nonetheless, the most important limitation of the project is the relatively small number of data points for computational modelling.
^
113

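### The 14 actigraphy days lie inside the 26-week relapse window, and the plan does not say how relapse models treat later epochs that start in an episode

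*Protocol article*

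**What the plan says.** **Recording window.** In Study 1, "individuals with BD will wear actigraphs for 14 days at the start of each of three consecutive 26-week monitoring epochs" (section 2.2). The abstract agrees: "Each epoch commences with 14 days of actigraphy, followed by retrospective interviews at 13 and 26 weeks". Study 2 repeats the design with one epoch.

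**Outcome window.** Under section 2.4, "LIFE interviews will occur twice in each monitoring epoch (13 weeks, and 26 weeks, with 13 weeks’ retrospection window at each interview". The week-13 interview therefore covers the recording days. Section 2.2 describes the whole span as forecasting time: "for a total window of 3 × 26 = 78 weeks forecasting". The Discussion counts "7 days X 26 weeks X 3 epochs X 100 participants = up to 54,600 follow-up days" alongside "14 days X 3 epochs X 100 participants = up to 4,200 actigraphy days". The secondary symptom-burden outcome is also taken over the full epochs.

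**Episode status.** Section 2.7 states that "meeting MADRS or YMRS episode criteria (> 12 and > 8, respectively) is an exclusion criterion at baseline". Section 2.1 adds: "Meeting episode criteria at one of the follow-up interviews is, however, not an exclusion criterion". Section 2.7 provides for team review at follow-up, with a possible four-week pause and re-assessment or a decision that the person cannot continue, each case by case.

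**Definition and use.** Section 2.6 defines relapse as a newly starting mood episode that satisfies DSM-5, and uses the outcomes to label actigraphy epochs for model training. It also says that the Complex System Model should learn features that come before a transition.

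**The concern.** A forecast needs the predictor to be measured before the event. If someone relapses on day 5, the 14-day recording holds about nine days of that episode, yet it is used to predict it. Part of any apparent forecasting skill is then recognition of an episode already under way. This works against the early-warning aim, and the Work Package 4 meta-model would inherit it.

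The second issue arises because the Study 1 epochs are contiguous and episode-free status is required only at study baseline. The next recording follows directly on the week-26 interview, so it can be made during an episode. The text does not say whether such an epoch belongs in the relapse risk set or how it is labelled. Disrupted rhythms caused by a current episode could then be read as an interepisode predictor.

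**Working it through.** **1. Reproduce the plan's figures.**
- Follow-up days: 7 × 26 × 3 × 100 = 54,600, as stated.
- Without the recording days: 7 × 24 × 3 × 100 = 50,400. The difference is 4,200, which is the protocol's own actigraphy-day total (14 × 3 × 100). The recording days are therefore counted as follow-up.
- Expected relapses: 0.4 per year × 1.5 years × 100 = 60, as stated in the Discussion, again over the full 78 weeks.

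**2. Onsets inside the recording windows** (constant hazard λ = 0.4/52 per week).
- Share of each epoch: 14/182 = 7.7%.
- All relapses: 60 × 6/78 = 4.6.
- First relapses overall: 100 × (1 − exp(−0.6)) = 45.1.
- First relapses in the windows: 100 × (1 − exp(−2λ)) × (1 + exp(−0.2) + exp(−0.4)) = 1.527 × 2.489 = 3.8, or 8.4% of first relapses.
- Study 2: 25 × 0.4 × 0.5 = 5 expected relapses, of which 5 × 2/26 = 0.4 fall in the window.

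**3. Size of the bias from overlap alone.** I simulated one epoch of 100 people with no true effect. The recorded value shifts by d SD times the fraction of the 14 days that follow onset (400 runs). The values of d are assumptions.

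| d (SD) | Apparent HR, risk from day 1 | Apparent HR, risk from day 15 |
|---|---|---|
| 0 | 1.01 | 1.01 |
| 0.5 | 1.03 | 1.02 |
| 1 | 1.04 | 0.99 |
| 2 | 1.09 | 1.01 |

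Simulation noise is about 0.01 to 0.02. A three-epoch simulation with shifts of 0.5 to 1 SD gave an AUC of 0.51 from overlap alone, against 0.50 with the later start.

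**4. Epochs 2 and 3 starting in an episode.** There are 2 × 100 = 200 later epoch starts. Simulation alternated well time (rate 0.4 per year) with exponentially distributed episodes. The documents give no episode length, so a range is shown, before any pause or withdrawal.

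| Assumed mean episode length | Starts in an episode, of 200 |
|---|---|
| 4 weeks | 6 |
| 8 weeks | 11 |
| 13 weeks | 17 |
| 26 weeks | 27 |

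**5. Cost of starting on day 15.** Events: 60 × 24/26 = 55.4 in all, or 45.1 − 3.8 = 41.3 first relapses. Power by the Schoenfeld approximation is Φ(√D × ln 1.57 − 1.96), with two-sided 0.05 assumed:
- all relapses: D = 60 gives 93.7%; D = 55.4 gives 91.9%;
- first relapses: D = 45.1 gives 85.8%; D = 41.3 gives 82.6%.

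The stated 90.6% corresponds to about 52.8 events on this formula. The baseline hazard behind the protocol's simulation is not given, so its figure can be neither confirmed nor refuted. The differences above are the useful part.

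**The case against.** **Deferred detail.** Time zero is not stated in words. The article leaves analytic detail to a forthcoming analysis plan and study-level protocols, and Figure 1 and the footnotes are not shown. Any of these could hold a landmark rule. That limits certainty, but the article itself fixes the look-back, the 78 weeks and the follow-up days without one, and a later rule would have to depart from those statements.

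**Carried-over episodes.** A reader might infer that an episode running from one epoch into the next is scored as a forecast of itself. The documents do not support this, because relapse means a new onset. If carried-over episodes were labelled positive, simulation with no true effect gives AUCs of 0.53 to 0.58, but the plan states no such labelling. In the time-to-first-relapse analysis, someone in an episode at the start of epoch 2 or 3 has normally already had the event. Case-by-case pause or removal would also lower the counts in step 4. All of this stands. What remains is in the recurrent-event models and the models trained on labelled epochs.

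**Small effect.** Fewer than five relapses are affected by the overlap, some of those recordings are partly pre-onset, and the project calls itself exploratory. This also stands, and it sets the weight of the point.

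**Network analysis.** Dynamic Bayesian Network work aims to follow how symptoms and rhythms change together, so dropping in-episode epochs there would discard intended data. This stands, and the fix respects it.

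**Conclusion.** The point holds in a limited form. In Studies 1 and 2 the predictor window sits inside the outcome window. At 0.4 episodes per year and a constant hazard, about 4.6 of 60 Study 1 relapses, or 3.8 of about 45 first relapses, would start during recording. With assumed shifts of 1 to 2 SD, the apparent hazard ratio under no true effect is about 1.04 to 1.09, small beside the planned 1.57 but towards false prediction in a dataset with few events. For symptom burden the overlap is direct, since the recording weeks count in the outcome.

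For Study 1 epochs that start in an episode, the supportable statement is that their place in the relapse risk set and their label are undefined. It is not that they are counted as successful forecasts. Their number rests wholly on assumed episode lengths.

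**What to change.** Settle these rules before any model is trained:
- For relapse-prediction models, start time at risk on day 15 of each epoch. Start the symptom-burden window there too. LIFE ratings are weekly, so this means 24 of the 26 weeks and no new data.
- Report onsets in days 1 to 14 separately, as episodes detected during recording.
- Admit an epoch to the relapse risk set only if LIFE shows no episode during its recording or at the day-15 landmark. Otherwise set it aside until the next epoch, with a sensitivity analysis that includes it.
- Keep all epochs in Dynamic Bayesian Network analyses of how symptoms and rest-activity rhythms evolve.
- Restate Study 1 forecast follow-up as 72 weeks and up to 50,400 days, with about 55 expected relapses.

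These are analysis rules only and leave the case-by-case review of participants as it is. The day-15 start costs about 8% of events, with the power changes in step 5 of the working. Those figures do not include relapses lost with epochs that are set aside; that further loss depends on episode length.
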